**Objective:**

The primary objective of this study is to demonstrate noninferiority of an ultrashort, 1-month TPT regimen of isoniazid plus rifapentine, administered 3 times a week (1H_3_P_3_) compared with the standard 3-month daily isoniazid plus rifampicin (3HR) regimen in preventing active TB, as measured by the 24-month cumulative incidence of active TB following randomization.

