### TPT Intervention

Eligible participants, clustered by epidemiologically linked index cases, will undergo 1:1 randomization through an interactive web response system into 2 arms: the intervention arm will receive a 12-dose 1H_3_P_3_ regimen, and the active control arm will receive a 90-dose 3HR regimen. Intervention discontinuation should be considered under the following circumstances: (1) at any time upon request by the participant and/or their guardian, (2) major protocol deviation, or (3) an AE deemed by the safety review committee to result in an unfavorable risk-benefit profile for the participant. Interruption of one or more drugs of the assigned regimen consecutively for ≥1 month will be considered permanent discontinuation. Table 1 shows the detailed dosage and administration protocol of study drugs in each regimen. Any dose adjustment is strictly prohibited and will be considered a protocol deviation. All medications will be provided free of charge. TPT other than the assigned intervention is prohibited during the study.

**Table 1. T1:** Dosage and administration of study drugs for the 1H_3_P_3_ (1-month isoniazid plus rifapentine 3 times weekly) and 3HR (3-month daily isoniazid plus rifampicin) regimens.

Regimen and dosing categories (age and/or weight)	Dosage			Administration	Treatment course (months)
	Isoniazid	Rifapentine	Rifampicin		
1H_3_P_3_					
Weight 30-35 kg	300 mg	300 mg	N/A^a^	3 times weekly	1
Weight ≥35 kg	400 mg	450 mg	N/A	3 times weekly	1
3HR					
Age ≥18 years					
Weight <50 kg	300 mg	N/A	450 mg	Once daily	3
Weight ≥50 kg	300 mg	N/A	600 mg	Once daily	3
Age <18 years (weight-based dosing)	10 mg/kg^b^	N/A	10 mg/kg^c^	Once daily	3

a N/A: not applicable.

b Maximum dose of isoniazid=300 mg.

c Maximum dose of rifampicin=450 mg.

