Treatment adherence			✓	✓	✓	✓			
Safety monitoring			↔	↔	↔	↔	↔		
Tuberculosis surveillance		↔	↔	↔	↔	↔	↔	↔	↔

a This row displays specific time points relative to randomization. Acceptable time window: more or less than 7 days for the intervention period and more or less than 30 days for the postintervention phase.

b ↔: this arrow represents continuous interventions.

c On-treatment assessments and 1-month posttreatment assessments require in-person attendance, whereas postintervention assessments may be conducted in person or remotely.

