### Study Objectives and End points

The primary objective is to demonstrate noninferiority of the ultrashort course of the 1H_3_P_3_ TPT regimen compared with the standard 3HR regimen in preventing active TB, as measured by the 24-month cumulative incidence of active TB following randomization. The secondary objectives include: (1) to compare safety, patient-reported quality of life, and treatment discontinuation rates attributable to AEs between the regimens; (2) to evaluate treatment adherence using protocol-defined completion criteria; (3) to assess acquired *M tuberculosis* drug resistance among participants who develop active TB after TPT; and (4) to establish a contemporary nonintervention cohort for exploratory comparison, delineating the natural progression to active TB among individuals with high-risk LTBI in whom active TB has been ruled out.

The primary end point is a composite of bacteriologically confirmed or clinically diagnosed active TB within 24 months after randomization. Bacteriologically confirmed active TB refers to *M tuberculosis* identification via ≥1 sputum culture and/or molecular assay (eg, GeneXpert MTB-RIF) with detectable bacterial load. Clinically diagnosed TB combines objective clinical symptoms (≥2 of the following: cough ≥2 weeks, fever, night sweats, weight loss >10%, or hemoptysis) and imaging findings highly suggestive of active TB (eg, cavity or nodular lesions on chest CT), after exclusion of alternative diagnoses. Secondary end points include severity-graded AEs, treatment discontinuation (defined as any permanent cessation prior to regimen completion), treatment completion (defined as completing ≥90% of scheduled doses within 110% of the planned treatment duration), all-cause mortality, and acquired drug resistance determined by drug susceptibility testing or targeted molecular assays of *M tuberculosis* isolates from active TB cases. Exploratory analysis will use the nonintervention cohort to establish the background incidence of active TB, against which the risk reduction of each TPT regimen can be calculated. Patient-reported outcomes (PROs) will be calculated using health state utility values and EuroQol visual analog scale scores.

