### Statistical Analysis

Statistical analyses will be performed using SAS and R (R Foundation for Statistical Computing). Multiple imputation will be conducted to handle missing data, with additional inverse probability weighting applied for the nonintervention cohort to adjust for potential attrition bias. Continuous variables will be summarized as mean (SD) or median (IQR), as appropriate. Categorical variables will be summarized as counts and percentages.

The primary analysis will assess the noninferiority of the 1H_3_P_3_ regimen compared to the 3HR regimen in preventing active TB over the 24-month follow-up period, and the primary end point is the composite of bacteriologically confirmed or clinically diagnosed active TB. To account for the cluster randomized design and the inherent correlation within clusters, we will use a Cox proportional hazards regression model with shared frailty terms and exact likelihood estimation. Noninferiority of the 1H_3_P_3_ regimen relative to the 3HR regimen will be concluded if the analysis demonstrates that the 1H_3_P_3_ regimen does not experience a ≥20% relative reduction in protective efficacy for preventing active TB over the 24-month follow-up period. To enhance precision and address potential baseline imbalances despite randomization, the model will adjust for key prespecified covariates, such as age, sex, BMI, characteristics of the index case (smear or cavitation status), and cluster size. Outcomes will be assessed via 2 prespecified analyses with explicit definitions: the modified intention-to-treat population includes all randomized participants who received at least 1 dose of the study medication, analyzed by the assigned treatment group regardless of subsequent protocol deviations or treatment discontinuation; the per-protocol population includes all randomized participants who completed ≥90% of scheduled doses within 110% of the planned treatment duration without major protocol deviations (including use of prohibited concomitant anti-TB medications, enrollment despite exclusion criteria, or unblinding to outcome assessors). Prespecified subgroup analyses will examine treatment effect heterogeneity by age (13-17 years vs ≥18 years) and index case features (smear or cavitation status), tested through interaction terms in Cox models (interaction *P*<.10).

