For secondary end points, all AEs, serious AEs (SAEs), and treatment discontinuations due to AEs will be documented. Group differences in AE proportions will be analyzed using the chi-square test or Fisher exact test (2-sided *α*=.05). Treatment completion is defined as consuming ≥90% of planned doses within 110% of the planned treatment duration (≥11 doses within 6 weeks for the 1H_3_P_3_ group and ≥81 doses within 16 weeks for the 3HR group). The 2-year cumulative incidence of active TB in the nonintervention cohort will be calculated using the Kaplan-Meier method, with 95% CI estimated. The protective efficacy of the 1H_3_P_3_ and 3HR regimens relative to the nonintervention cohort will be quantified as the risk reduction rate: 1–(intervention group incidence/nonintervention group incidence). The Fisher exact test will be used to compare incidence differences among the 3 cohorts.

All analyses concerning the PRO end point will be explicitly restricted to the subgroup of participants who complete the EuroQol 5-Dimensions 3-level questionnaire. The baseline characteristics of this PRO subgroup will be compared between the 2 arms to confirm that randomization balance was maintained. Any interpretation of PRO findings will explicitly acknowledge their exploratory nature and the fact that they are derived from a subset of the total study population. Trends in PRO metrics over time will be visualized using line graphs, with mean values and 95% CIs plotted to illustrate group-level changes. A mixed-effects model for repeated measures will be used to compare PRO differences between the 1H_3_P_3_ and 3HR groups across time points, with fixed effects including treatment group, assessment time point, treatment group×time point interaction, age, sex, BMI, and index case cavitation status, and a random participant-specific intercept to account for within-subject correlation from repeated assessments.

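### The 6-week and 16-week limits given for treatment completion do not equal the 110% of planned duration they are meant to express, and it is unclear which limit will define the per-protocol set

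*Protocol article*

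**What the plan says.** All references are to the Protocol article.

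- **Planned courses.** TPT Intervention: "the intervention arm will receive a 12-dose 1H_3_P_3_ regimen, and the active control arm will receive a 90-dose 3HR regimen". The Abstract's Objective describes the experimental arm as a "1-month TPT regimen of isoniazid plus rifapentine, administered 3 times a week" and the control as the "standard 3-month daily isoniazid plus rifampicin (3HR) regimen". Table 1 gives the courses as 1 and 3 months. No planned length in days is given.
- **Completion, end point section.** Study Objectives and End points: "completing ≥90% of scheduled doses within 110% of the planned treatment duration". No week limits appear here.
- **Completion, analysis section.** Statistical Analysis, secondary end points: "Treatment completion is defined as consuming ≥90% of planned doses within 110% of the planned treatment duration", followed in parentheses by "≥11 doses within 6 weeks for the 1H_3_P_3_ group and ≥81 doses within 16 weeks for the 3HR group".
- **Per-protocol population.** Statistical Analysis: participants who "completed ≥90% of scheduled doses within 110% of the planned treatment duration without major protocol deviations". No week limits appear here either.

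**The concern.** The parenthesis is written as the working form of the 110% rule, yet 6 and 16 weeks are visibly longer than 110% of 1 and 3 months. One sentence then holds two rules, and a programmer could follow either.

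The participants whose status depends on the choice are those who reach the required dose count after the 110% limit but before the week limit: the 11th dose after roughly day 31-34 and by day 42 in the 1H3P3 arm, and the 81st dose after roughly day 99-101 and by day 112 in the 3HR arm.

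Two results are exposed. Completion is a named secondary end point, and better completion is the main practical benefit claimed for the short regimen in the Conclusions and Discussion. The per-protocol analysis is one of only two prespecified analyses in a noninferiority trial, and its membership rule uses the same 90%/110% wording. The trial is open label, so the choice should be settled before outcomes by arm are seen.

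**Working it through.** **Inputs.** Doses: 12 and 90 (TPT Intervention). Frequency: 3 per week and daily (Abstract, Table 1). Length: 1 and 3 months (Table 1). Limits: 6 and 16 weeks (Statistical Analysis). The document gives no length in days, so a range is used. For 1H3P3 it is 28 days (12 doses / 3 per week = 4 weeks) to 31 days (a calendar month). For 3HR it is 90 days (90 daily doses) to 92 days (three calendar months).

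**Step 1: dose counts.** 0.90 × 12 = 10.8, rounded up to 11. 0.90 × 90 = 81. Both stated counts are reproduced.

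**Step 2: duration limits.** Limit at 110% = 1.10 × planned days. Stated limit as a percentage = 7 × weeks / planned days.

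| Arm | Planned days | 110% limit | Stated limit | Stated / planned |
|---|---|---|---|---|
| 1H3P3 | 28 | 30.8 | 42 | 150% |
| 1H3P3 | 30 | 33.0 | 42 | 140% |
| 1H3P3 | 31 | 34.1 | 42 | 135% |
| 3HR | 90 | 99.0 | 112 | 124% |
| 3HR | 92 | 101.2 | 112 | 122% |

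Rounded up to whole weeks, the 110% limits are 5 weeks (30.8/7 = 4.4 to 34.1/7 = 4.9) and 15 weeks (99/7 = 14.1 to 101.2/7 = 14.5), not 6 and 16. Reading 3 months as 12 weeks (84 days) makes the 3HR figure 112/84 = 133%, which is further from 110%. No reading gives 110% in either arm.

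**Step 3: comparison between arms.**

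- Share of planned duration: 135-150% for 1H3P3 against 122-124% for 3HR.
- Required dosing rate at 110% (28- and 90-day plans): 4.4 weeks × 3 = 13.2 slots, so 11/13.2 = 83%, against 81/99 = 82%. The arms are nearly equal.
- Required dosing rate under the week limits: 6 × 3 = 18 slots, so 11/18 = 61%, against 81/112 = 72%.
- Extra days beyond plan: 42 − 31 = 11 to 42 − 28 = 14 for 1H3P3, against 112 − 92 = 20 to 112 − 90 = 22 for 3HR.
- Dose threshold: 11/12 = 91.7% (one missed dose allowed) against 81/90 = 90% (nine allowed).

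The first and third comparisons are more lenient to 1H3P3. The last two are more lenient to 3HR.

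**Step 4: where the difference would show (illustration only).** Assume that each dose slot is used independently with the same probability and that missed doses can be made up within the limit; the document states neither. The chance of counting as complete is then a binomial tail: at least 11 of 18, or at least 81 of 112.

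| Slot adherence | 1H3P3 | 3HR |
|---|---|---|
| 70% | 0.86 | 0.34 |
| 75% | 0.94 | 0.78 |
| 80% | 0.98 | 0.98 |

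Above 80% the arms stay about equal, so the difference matters mainly at moderate adherence.

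**The case against.** **A grace period may explain the figures.** A footnote to Table 2 reads "Acceptable time window: more or less than 7 days for the intervention period". Adding 7 days to the 110% limits gives 37.8 to 41.1 days and 106 to 108.2 days, which round up to exactly 6 and 16 weeks. This is a plausible origin, and it suggests an undocumented allowance as readily as a deliberate choice. But the footnote concerns assessment time points, the article does not apply it to treatment duration, and the end point and per-protocol definitions would still say 110%. A fixed 7 days is also a larger share of the short course (7/28 = 25%) than of the long one (7/90 = 8%).

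**Direction.** A reader might infer that the week limits simply favour the experimental arm, or that they add a definite number of points to the completion difference. The document does not support either. The advantage exists on the relative scale and in required dosing rate; in absolute days and dose threshold 3HR has the easier terms. The article does not say how many participants would finish between the two limits in either arm, so any figure in percentage points would be an assumption.

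**Reach.** A reader might also infer that the per-protocol set has two contradictory rules. It does not: its definition gives only the 110% wording. What stands is that a reader cannot tell whether the week limits, offered as the meaning of identical wording, will be applied there.

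**Conclusion.** The inconsistency stands as an arithmetic fact and does not depend on how a month is counted. The stated limits are about 135-150% (1H3P3, 28 to 31 days) and 122-124% (3HR, 90 to 92 days) of planned duration, where the rule says 110%. The 150% figure is the upper end and requires a 28-day course.

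The completion end point has two conflicting rules, and the limit for the per-protocol set is uncertain. Under the week limits the arms are not held to the same relative standard, but the effect on the results cannot be sized from the document. The modified intention-to-treat population requires only one dose, so that analysis is not touched. This is a should-fix point.

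**What to change.** Before any outcome by arm is reviewed:

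1. State the planned duration of each regimen in days.
2. Reconcile Study Objectives and End points, the per-protocol definition and the secondary end point paragraph of Statistical Analysis to one rule, with an explicit day limit per arm derived from the same multiple of planned duration. If 110% is kept, the limits fall at about 31-34 and 99-101 days, depending on step 1. If a grace period was intended, it has to be written into the rule.
3. Apply that rule to both the completion end point and the per-protocol set.

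A sensitivity analysis under the other reading is optional. The cost is wording and programming only: the medication diary already records the time of each dose, and by the article's own timeline analysis begins only after the 2-year follow-up. If the shorter limits are adopted, completion percentages may be slightly less favourable.

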#### Enrollment of LTBI Contacts

Contacts testing positive on QuantiFERON-TB Gold Plus (QIAGEN N V) will subsequently receive chest computed tomography (CT) or chest X-ray, as well as pooled sputum nucleic acid amplification testing (eg, GeneXpert MTB-RIF [Danaher Corp]) to exclude active TB. LTBI is defined as a positive interferon-gamma release assay result without evidence of active TB. Those with confirmed LTBI and aged ≥13 years are eligible for this trial. Study protocols will be thoroughly explained to eligible participants by site investigators, with written informed consent obtained prior to enrollment. Parental or guardian consent is mandatory for minors (aged <18 years). Participants meeting the inclusion criteria but declining enrollment in the TPT trial will be invited to join a supplemental nonintervention cohort. After providing separate informed consent, they will be followed for 24 months to monitor for the development of active TB. Further eligibility validations will require review of medical history and comprehensive laboratory evaluations to exclude contraindications to TPT. Textbox 1 shows the detailed inclusion and exclusion criteria.

Textbox 1.Inclusion and exclusion criteria for the TB-YOUTH study.

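### The exploratory efficacy estimate against the nonintervention cohort is unadjusted for confounding, and the only weighting planned for that cohort addresses attrition, not self-selection

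*Protocol article*

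**What the plan says.** All references are to the protocol article.

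- **Who the comparators are** (Enrollment of LTBI Contacts): "Participants meeting the inclusion criteria but declining enrollment in the TPT trial will be invited to join a supplemental nonintervention cohort". They give separate consent and are followed for 24 months. The next step in the same paragraph reads "Further eligibility validations will require review of medical history and comprehensive laboratory evaluations to exclude contraindications to TPT"; the text does not say whether decliners go through it.
- **Purpose** (Study Objectives and End points): the cohort is set up under the fourth secondary objective, for an exploratory comparison. It is to supply a background incidence "against which the risk reduction of each TPT regimen can be calculated".
- **Estimator** (Statistical Analysis): "The 2-year cumulative incidence of active TB in the nonintervention cohort will be calculated using the Kaplan-Meier method", with a 95% confidence interval. The efficacy of the "regimens relative to the nonintervention cohort will be quantified as the risk reduction rate", given as "1–(intervention group incidence/nonintervention group incidence"). A Fisher exact test compares the three cohorts.
- **Weighting** (Statistical Analysis): multiple imputation is planned for missing data, "with additional inverse probability weighting applied for the nonintervention cohort to adjust for potential attrition bias".
- **Covariates** (Statistical Analysis): the randomized Cox model adjusts for age, sex, BMI, index-case features and cluster size, among others. The model for the patient-reported outcomes also lists its covariates. None are listed for the comparison with the nonintervention cohort.

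**The concern.** The randomized arms differ only by chance, yet their comparison receives covariate adjustment. The nonintervention cohort differs from both arms by choice: its members refused the trial and then agreed to be followed. Nothing in the stated estimator or test allows for that. Attrition weights let those who remain in the cohort stand in for those who left it. They cannot make people who declined resemble people who enrolled.

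The groups may also differ beyond choice. Textbox 1 keeps out of the trial people with HIV, people on immunosuppressive therapy and contacts of index cases with documented isoniazid or rifampicin resistance. Decliners are described only as meeting the inclusion criteria. The Introduction itself says that incidence is higher in immunocompromised people. If such people enter the nonintervention cohort, its incidence rises and each regimen looks more effective than it is. If decliners instead had lighter exposure, the error runs the other way.

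At stake is the trial's only internal estimate of what either regimen achieves against no treatment. It will be reported as protective efficacy and is likely to be read as the regimen's true effect. The analysis section attaches an explicit caution to the patient-reported results but none to this figure, and the limitations in the Discussion do not mention self-selection.

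**Working it through.** **Inputs** (Randomization and Sample Size Calculation): 2-year incidence without treatment 7%; assumed efficacy of both regimens 70%; 2-year incidence on either regimen 2.1%.

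**Step 1, the plan's own figure.** Its formula gives 1 − 0.021/0.07 = 0.70, so the stated 70% reproduces.

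**Step 2, let decliners differ.** Hold true efficacy at 70%, so that participants have 7% risk untreated and 2.1% treated. Let the decliners' untreated risk be k × 7%. The plan's estimator then returns

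apparent efficacy = 1 − 0.021/(0.07 × k).

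The documents give no value for k, so the range below is an assumption.

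| k | Decliners' incidence | Apparent efficacy | Shift from 70% |
|---|---|---|---|
| 0.8 | 5.6% | 1 − 0.021/0.056 = 62.5% | −7.5 points |
| 0.9 | 6.3% | 1 − 0.021/0.063 = 66.7% | −3.3 points |
| 1.0 | 7.0% | 70.0% | 0 |
| 1.1 | 7.7% | 1 − 0.021/0.077 = 72.7% | +2.7 points |
| 1.25 | 8.75% | 1 − 0.021/0.0875 = 76.0% | +6.0 points |

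**Step 3, do the planned weights help?** They model remaining under follow-up within the nonintervention cohort. Suppose nobody is lost. The weights are then all equal, the cohort's estimated incidence is still k × 7%, and every shift in the table stands. The Fisher exact test takes no covariates, so it carries the same bias.

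**The case against.** **The comparison is exploratory.** That is so: no decision rule, alpha or sample size rests on it. This lowers the weight of the point but does not make the estimator sound.

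**Details of weighting belong in the SAP.** The list of weight covariates commonly does. Here, however, the article states the estimator, the test and the purpose of the weights. The point is about a stated method, not a missing detail.

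**The inclusion criteria already limit differences.** They require age 13 or over, confirmed infection and more than 4 hours of shared exposure in a week. This narrows the differences in exposure but does not remove selection by choice.

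**The estimate is not wholly crude.** The nonintervention incidence is a Kaplan-Meier estimate, and imputation covers missing data generally. That stands; the accurate description is unadjusted for confounding.

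Three stronger readings are tempting and are not supported:

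- A reader might infer that the error can reach the whole noninferiority margin. The 20% relative margin takes 70% to 0.8 × 70% = 56%, and apparent efficacy equals 56% when k = 0.021/(0.44 × 0.07) = 0.68. That value is solved for, not documented. It is neither a bound nor a likely value.
- A reader might infer that the noninferiority decision is biased, because its criterion also speaks of protective efficacy. The primary analysis is a Cox model between randomized arms, and self-selection of decliners does not bias that hazard ratio. The article does not say that the nonintervention incidence enters the decision.
- A reader might infer that these people refused preventive treatment because of how they saw their own risk. The article says only that they declined the trial. A link with perceived risk is plausible but undocumented.

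**Conclusion.** The point holds for the exploratory comparison only. Followed as written, the plan yields an efficacy figure for each regimen that is confounded by the choice to decline, and its stated weighting does not address this. The direction is unknown. For underlying risks that differ by 10% to 25%, the figure moves by roughly 3 to 8 points (62.5% to 76% around a true 70%).

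This rests on the plan's 7% and 2.1%, on an assumed k between 0.8 and 1.25, and on the nonintervention cohort remaining untreated, as its name implies. The flaw is worth correcting because the figure is likely to be quoted as the regimens' efficacy, but it leaves the trial's primary conclusion untouched.

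**What to change.** Make the main estimate of this exploratory comparison an adjusted one:

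1. **Participation weights.** Model the probability p of enrolling rather than declining, on variables available for both groups: age, sex, student or staff, site, and index-case smear and cavitation status. Weight each decliner by p/(1 − p), so that the cohort is standardized to the randomized population. The article does not confirm that BMI is recorded for decliners, so include it only if it is.
2. **Same exclusions.** Restrict the comparison to decliners who meet the trial's exclusion criteria as participants do, where the data allow. The article does not confirm that decliners have the history and laboratory review.
3. **Same attrition handling** in all three groups.
4. **Unadjusted ratio** kept as a descriptive line.
5. **Sensitivity range** for residual confounding. If decliners' remaining risk ratio is k, the corrected efficacy is 1 − k × (1 − estimated efficacy). An estimate of 70% becomes 1 − 0.8 × 0.30 = 76% at k = 0.8 and 1 − 1.25 × 0.30 = 62.5% at k = 1.25.

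A shared frailty for the index case should not be relied on for this purpose, because it is normally assumed independent of the covariates and so does not remove confounding by index case. Stratifying by index case would, but few strata would be informative: with 4 participants per cluster at 2.1%, about 1 − 0.979⁴ = 8% of clusters would contain any treated case, taking cases as independent.

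The cost is wording in the analysis plan and modest programming. The downside is somewhat wider intervals if the nonintervention cohort is small or the weights vary much. Recruitment is expected to run to September 2026 and analysis follows the 2-year follow-up, so the change can be fixed before any analysis.

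### The exploratory efficacy figures compare randomized participants with people who declined the trial, and the plan weights for attrition but not for who declines

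*Protocol article*

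**What the plan says.** The protocol article, under Enrollment of LTBI Contacts, forms the comparator as follows: "Participants meeting the inclusion criteria but declining enrollment in the TPT trial will be invited to join a supplemental nonintervention cohort". It continues: "After providing separate informed consent, they will be followed for 24 months to monitor for the development of active TB". The section then turns to the checks for contraindications: "Further eligibility validations will require review of medical history and comprehensive laboratory evaluations to exclude contraindications to TPT".

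Study Objectives and End points lists this cohort under the secondary objectives but calls the comparison exploratory. The cohort is to supply the background incidence from which each regimen's risk reduction is calculated.

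Statistical Analysis fixes four things for this comparison:

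- **Denominator.** "The 2-year cumulative incidence of active TB in the nonintervention cohort will be calculated using the Kaplan-Meier method, with 95% CI estimated".
- **Estimator.** Protective efficacy "relative to the nonintervention cohort will be quantified as the risk reduction rate", written out as 1 minus the intervention group's incidence divided by the cohort's incidence.
- **Weights.** Besides multiple imputation for missing data, "additional inverse probability weighting applied for the nonintervention cohort to adjust for potential attrition bias".
- **Test.** "The Fisher exact test will be used to compare incidence differences among the 3 cohorts".

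The same section lists adjustment for age, sex, BMI, index-case smear or cavitation status and cluster size, but for the Cox frailty model that compares the two randomized arms.

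**The concern.** People enter the cohort through two choices of their own: they refuse preventive treatment in the trial, and they agree to be followed without it. Either choice may be related to TB risk, for example through closeness of exposure, age, school or general health. A ratio of participants' incidence to decliners' incidence therefore combines the effect of the drugs with the difference between those who accept and those who refuse.

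The stated weights address another problem. Attrition weights make the decliners who stay under observation represent all decliners who joined. They do not make decliners represent the randomized participants.

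At stake are the only planned estimates of each regimen's efficacy against no treatment. The article takes more care with its other exploratory analysis, that of patient-reported outcomes. There it plans a baseline comparison of the groups, a covariate-adjusted model and an explicit caveat, although those groups are randomized. The efficacy comparison has none of these beyond the exploratory label, and the limitations in the Discussion do not mention selection into the cohort.

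**Working it through.** **1. The plan's own figure.** Randomization and Sample Size Calculation gives an untreated 2-year incidence of 7% and an assumed efficacy of 70%, hence 2.1% under treatment. The stated formula gives 1 − 0.021/0.07 = 0.70, so it reproduces the planning value when decliners and participants have the same untreated risk.

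**2. Effect of selection.** Let k be the decliners' untreated risk divided by the risk that participants would have had untreated. The documents give no value for k; the range 0.5 to 2 is an assumption. The reported efficacy is then 1 − 0.021/(0.07 × k) = 1 − 0.30/k.

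| k (assumed) | Decliners' 2-year risk | Reported efficacy when the truth is 70% |
|---|---|---|
| 0.5 | 3.5% | 40% |
| 0.8 | 5.6% | 62.5% |
| 1 | 7.0% | 70% |
| 1.25 | 8.75% | 76% |
| 1.5 | 10.5% | 80% |
| 2 | 14.0% | 85% |

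For a regimen with no effect the formula returns 1 − 1/k: +20% at k = 1.25 and −25% at k = 0.8.

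**3. Attrition weights leave k unchanged.** With perfect attrition weights, the cohort's Kaplan-Meier estimate recovers 0.07 × k, the risk of everyone who joined the cohort. The factor k remains in the denominator.

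**4. The randomized contrast.** Both efficacy figures share one denominator D. With arm incidences A and B, (1 − efficacy in arm A)/(1 − efficacy in arm B) = (A/D)/(B/D) = A/B. The incidence ratio between the arms does not depend on the cohort, and the Cox model does not use it.

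**5. The Fisher test beside the rest of the plan.**

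- *Censoring:* the cohort's incidence is a Kaplan-Meier estimate and 10% attrition is planned for. Fisher's test needs a simple yes/no count per person.
- *Weights:* they are specified for the cohort, but Fisher's test takes none.
- *Clustering:* the sample size uses an ICC of 0.05 and a mean cluster size of 4, so the design effect is 1 + (4 − 1) × 0.05 = 1.15. Fisher's test treats all persons as independent. On these values the understatement of variance within an arm is modest.
- *Hypothesis:* one test across three groups can reject because the decliners differ, because the two regimens differ, or both.

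**6. Who belongs to the cohort.** The enrollment text admits decliners on the inclusion criteria and mentions contraindication checks afterwards. The objectives say that active TB has been ruled out in the cohort, so at least one exclusion applies. Textbox 1 lists voluntary participation with signed consent as an inclusion criterion, which a decliner cannot literally meet. The text does not settle which exclusions apply.

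**The case against.** The strongest reply is that the analysis is labelled exploratory, that a full analysis plan may exist, and that the choice of weighting model is normally left to it. The label is there and limits the weight of the point. The second part carries less force, because the article itself states the estimator, the test and the purpose of the weights. Followed as written, it gives an estimate unadjusted for participation.

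Four stronger readings are tempting, and the documents do not support them.

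- *The noninferiority decision is biased.* A reader might infer this because the margin is expressed as a loss of protective efficacy. But the primary analysis is the Cox model of the two randomized arms, the planning values come from surveillance data and an assumption, and nothing says that the cohort's incidence enters the decision.
- *The figures are ratios of raw incidences.* The denominator is a Kaplan-Meier estimate and may carry attrition weights. What is missing is adjustment for participation.
- *People excluded from the trial remain in the cohort.* This rests on the order of sentences in a condensed paragraph, which need not be the order of procedures. It is an ambiguity.
- *Efficacy will be inflated.* Even if excluded people were present, only some exclusions, such as HIV infection or immunosuppression, would plausibly raise untreated risk. Resistance in the index strain need not, and prior treatment could lower it. No frequencies are given.

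It is also fair to say that no weighting can remove unmeasured reasons for refusal, and that the article does not show that BMI is recorded for decliners. Both limit the remedy, but neither justifies leaving measured differences unadjusted.

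**Conclusion.** The point holds for the exploratory efficacy comparison. It sets randomized participants against self-selected decliners with no stated adjustment for participation, and attrition weights cannot supply it. The accompanying Fisher test does not fit the censoring, weights and clustering that the plan handles elsewhere.

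The direction and size of the bias are unknown. The range of 40% to 85% around a true 70% illustrates an assumed twofold difference in untreated risk either way; it is not an estimate of the bias. The effect of clustering on the test is modest on the planning values. The change is worth making before the analysis, though the trial's main conclusion does not depend on it.

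**What to change.** In the Statistical Analysis text and the analysis plan:

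1. Estimate 24-month risks by Kaplan-Meier in all three groups.
2. In addition to the attrition weights, weight or standardize the decliners to the randomized participants on baseline variables available in both: for example age, sex, index-case smear and cavitation status and site, and BMI if it is recorded for decliners. Show the balance before and after.
3. Report 1 minus the weighted risk ratio for each regimen with a cluster-bootstrap confidence interval, resampling index cases so that participants and decliners linked to the same case stay together.
4. Drop the three-cohort Fisher test.
5. Label the result as a non-randomized comparison and name selection into the cohort among the limitations.
6. State which trial exclusions apply to the cohort. For this comparison, apply those that can be read from existing records.

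The cost is new wording and some analysis work, with no change to visits, treatment or randomization. Recruitment is projected to run to September 2026 and analysis follows the 2-year follow-up, so there is time. The price is wider intervals, a somewhat smaller cohort, and residual confounding from unmeasured reasons for refusal.
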